## Abstract

**Background:**

The use of a laryngeal mask airway (LMA) in appropriate patients supports fast-track anesthesia with a lower incidence of postoperative airway-connected adverse events. Data on the most favorable anesthetic in this context, with the lowest rate of upper airway complications and fast emergence times, are controversial and limited. Desflurane seems to match these criteria best, but large randomized controlled trials (RCTs) with a standardized study protocol are lacking. Therefore, we aim to compare desflurane with other commonly used anesthetics, sevoflurane and propofol, in a sufficiently powered RCT. We hypothesize that desflurane is noninferior regarding the frequency of upper airway events and superior regarding the emergence times to sevoflurane and propofol.

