### Outcomes

#### Primary outcome measures

The primary objective of this trial is to investigate, whether the emergence time until the stating of the date of birth after desflurane anesthesia is superior to the time after sevoflurane or propofol anesthesia. The selection of stating the date of birth as the primary clinical outcome variable is associated with the result of our latest meta-analysis [4]. This meta-analysis supposes faster emergence times in the desflurane-treated patients, but the included studies had only small sample sizes ≤65 patients per group. Furthermore, they were not all powered for this outcome variable, and the study protocols were not standardized for all patients. The time to state the date of birth was chosen, since this variable requires the most conscious answer compared to the other emergence variables. This primary outcome time variable is defined as time between cessation of anesthesia (T_0_) until the patient is able to state his/her date of birth on command (given every 20 sec.) and will be measured in minutes and seconds.

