### Sample size

Sample-size estimates for both considerations (superiority and noninferiority) were calculated separately. All sample sizes were calculated using a type 1 error, α = 0.05, and power of 0.80. The primary outcome calculations were carried out based on a one-way analysis of variance (same n) with three groups. The variances and means were estimated for the primary outcome variable time to state the date of birth from our meta-analysis [4]. For the sevoflurane, propofol and desflurane groups, means were set to 8.75, 6.8 and 5.6 minutes, respectively. A standard deviation of 3 minutes was considered (these parameters correspond to an effect size (f) of 0.43). A sample size of 19 patients per group is needed to detect such an effect for our superiority hypothesis.

The sample size for the noninferiority hypothesis was calculated based on the secondary outcome variable cough overall (CO). Using the normal approximation to the binomial and assuming a proportion of the outcome in the population between 0.07 and 0.10 and noninferiority bound of 0.20 a sample size of 81 and 112, respectively, is required to claim noninferiority. The margin delta of 20 % was chosen for clinical considerations. We claim that a difference of cough occurrence up to 20 % is clinically not relevant. This is justified by the result of our meta-analysis [4], where the identified coughs had never lead to a serious impact on the patients’ outcomes.

The sample size calculation for noninferiority of treatment is based on a sample size formula published by Blackwelder [7]. Considering data from the literature, a dropout rate of 5 patients per group (for example, requirement of endotracheal intubation, protocol deviations and losses for first postoperative day- follow up) is expected. We decided therefore to include 117 patients per group, to cover the calculated sample size of 19 + 5 patients per group for the superiority hypothesis as well as 112 + 5 patients for the noninferiority hypothesis. Altogether, there will be 351 randomized patients.

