### Statistical methods

All efficacy, safety and economical results will be presented on the Intention to Treat (ITT) data set, which will be composed of all randomized patients. In case it appears necessary, we will define a secondary Per Protocol (PP) data set prior to the database lock. The PP would be a subset of the ITT data set, composed of all randomized patients who have no major protocol deviations throughout their entire study period. This PP data set would be used for the secondary supportive analysis of the primary efficacy criterion and serve as a check of its robustness.

Parametric data will be analyzed with ANOVA and nonparametric data with the two-tailed Fisher’s exact test if incidence <5 or the Chi-square test with incidence >5. The inference for the noninferiority will be based on the upper confidence bound. A fully specified Statistical Analysis Plan will be made public before unmasking results. Additional analyses are not planned.

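### The superiority sample size of 19 per group is sized for an omnibus three-group ANOVA, not for desflurane against each comparator; 117 per group covers the pairwise need of 100, but the stated basis is wrong

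*Protocol article*

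**What the plan says.** The hypothesis in the abstract's Background is that desflurane is "superior regarding the emergence times to sevoflurane and propofol". The body words it differently. The primary question under Primary outcome measures is whether the emergence time after desflurane "is superior to the time after sevoflurane or propofol anesthesia", and Objectives and study design and Specific primary objective also join the comparators with "or".

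Under Sample size: "All sample sizes were calculated using a type 1 error, α = 0.05, and power of 0.80". Then: "The primary outcome calculations were carried out based on a one-way analysis of variance (same n) with three groups". The inputs follow: "For the sevoflurane, propofol and desflurane groups, means were set to 8.75, 6.8 and 5.6 minutes, respectively", with an SD of 3 minutes and an effect size f of 0.43. The conclusion is "A sample size of 19 patients per group is needed to detect such an effect for our superiority hypothesis". The number randomized, 117 per group, comes from the noninferiority calculation for cough (112 plus 5 dropouts). It is said to cover the 19 plus 5 for superiority as well.

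Statistical methods says "Parametric data will be analyzed with ANOVA" and defers full detail to a statistical analysis plan to be made public before unmasking. It does not name the comparisons of desflurane with each comparator.

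**The concern.** The question is directional and sets desflurane against named comparators. The test behind the 19 is neither: the omnibus F test rejects when any of the three means differ, in any direction. With the assumed means the F test is driven mainly by sevoflurane, which lies 3.15 min from desflurane, while propofol lies only 1.2 min from it. A size adequate for the F test can therefore be far too small for the harder of the two comparisons.

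At stake is the stated basis of the primary confirmatory claim. A reader of the sample size section would believe that 19 per group gives 80% power to show the superiority that the abstract describes. A reader of a positive F test might also take it as evidence that desflurane beats propofol, when it could arise from sevoflurane alone.

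**Working it through.** **Inputs** (Sample size section): means of 8.75 (sevoflurane), 6.8 (propofol) and 5.6 min (desflurane); common SD 3; α = 0.05; power 0.80; 117 per group with 5 dropouts, so 112 evaluable. Sidedness is not stated. Pairwise tests are taken as two-sided, with normal errors.

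**1. Reproduce the plan's figure.**
- Grand mean = (8.75 + 6.8 + 5.6)/3 = 7.05; deviations 1.70, −0.25, −1.45.
- f = √[(2.89 + 0.0625 + 2.1025)/3]/3 = √1.685/3 = 1.298/3 = 0.433, which agrees with the stated 0.43.
- Omnibus power uses the noncentral F with 2 and 3n − 3 df and noncentrality 3n·f².
- n = 18: noncentrality 10.11, power 0.795. n = 19: noncentrality 10.67, power 0.819.

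So 19 is the smallest n reaching 0.80 for the omnibus test.

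**2. Power for the pairwise comparisons at 19 per group.** Two-sample t test with 2n − 2 df and noncentrality (Δ/SD)·√(n/2).
- Desflurane vs sevoflurane: Δ = 8.75 − 5.6 = 3.15; noncentrality 1.05 × √9.5 = 3.24; power 0.88.
- Desflurane vs propofol: Δ = 6.8 − 5.6 = 1.2; noncentrality 0.40 × √9.5 = 1.23; power 0.22.
- Both significant in favour of desflurane (200,000 simulated trials, pooled ANOVA SD): about 0.22.

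The propofol figure is not sensitive to the choice of test: 0.23 with the pooled ANOVA SD, 0.23 by normal approximation, 0.33 if one-sided 0.05 was meant.

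**3. Size needed for the smaller contrast.** Normal approximation: n = 2(1.960 + 0.842)²/0.40² ≈ 98.1, which rounds up to 99. With the t distribution, 100 per group gives 0.80.

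**4. Power at the planned size.**

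| Per group | Desflurane vs propofol | Both contrasts |
|---|---|---|
| 19 | 0.22 | 0.22 |
| 112 | 0.85 | 0.85 |
| 117 | 0.86 | 0.86 |

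Power against sevoflurane is practically 1 at 112, so propofol alone determines the joint figure.

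**5. What a significant F test would mean at 112 per group.**
- Desflurane equal to propofol (means 8.75, 6.8, 6.8): f = 0.306, noncentrality 336 × 0.306² ≈ 31.5, power above 0.999.
- Desflurane 1.2 min slower than propofol (means 8.75, 6.8, 8.0): f = 0.268, noncentrality 336 × 0.268² ≈ 24.1, power 0.995.

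In both cases superiority to propofol is false, and the F test is still almost certain to be significant.

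**The case against.** **The 19 determines nothing, because 117 per group are randomized.** This stands. A reader might infer from the 0.22 that the trial is underpowered for its primary endpoint; the documents do not support that, since 112 evaluable patients give about 0.85. But the cover is a by-product of a secondary-endpoint calculation, and the sentence about 19 remains incorrect.

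**"Or" may mean that beating either comparator is enough.** Three sections of the body use it. On that reading 19 per group gives about 0.88 through sevoflurane, and the stated size is adequate. The abstract says "and", so the text does not settle the matter. The 0.22 is conditional on the "and" reading.

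**Contrasts belong in the statistical analysis plan.** Largely accepted. A reader might infer that the primary analysis cannot answer the primary question. The article does not support going that far: ANOVA is a model from which contrasts can be drawn, and nothing says that the F test alone decides superiority. The remark in Statistical methods that no additional analyses are planned may refer to exploratory work. What the unseen plan cannot mend is the affirmative statement about 19.

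**Inflated type I error.** A reader might infer this from two comparisons without adjustment. It does not follow from the text: requiring both comparisons to succeed causes no inflation, and with three groups a preceding significant ANOVA controls the familywise error even if either success counted.

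**Conclusion.** The point holds as an error in the stated basis of the primary sample size. The 19 is arithmetically right for an omnibus three-group ANOVA (power 0.82) and wrong as the size for showing desflurane faster than both comparators, where it gives about 0.22 and 100 per group are needed. It is not a shortage of patients.

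This rests on the protocol's own means and SD, two-sided tests at 0.05, and the abstract's "and". Under the "or" reading the number would suffice, but the article would still contradict itself about what counts as success. Under either reading, a significant F test alone does not show which group is faster.

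**What to change.** 1. Use one wording of the hypothesis in the abstract, Objectives and study design, Specific primary objective and Primary outcome measures: desflurane superior to sevoflurane and to propofol.
2. State that superiority is claimed only if both prespecified contrasts from the ANOVA model, desflurane-sevoflurane and desflurane-propofol, each two-sided 0.05, favour desflurane. Since both must succeed, α need not be split.
3. In Sample size, replace 19 by 100 per group, based on the 1.2 min desflurane-propofol difference with SD 3, and state that 112 evaluable per group give about 0.85 power for both contrasts.

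The cost is wording only, with no added patients, visits or data. The downside is a less favourable stated size (100 instead of 19). The success rule should be fixed before unmasking.

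### The stated 20-point noninferiority margin for cough does not yield 81 and 112 patients per group, so the margin and the calculation that sets the trial size must be reconciled.

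*Protocol article*

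**What the plan says.** The Sample size section of the protocol article gives these inputs for both hypotheses: "All sample sizes were calculated using a type 1 error, α = 0.05, and power of 0.80". For noninferiority on cough it uses the normal approximation to the binomial and the Blackwelder formula, "assuming a proportion of the outcome in the population between 0.07 and 0.10", and concludes with a "noninferiority bound of 0.20 a sample size of 81 and 112, respectively, is required to claim noninferiority".

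The margin is then repeated and defended: "The margin delta of 20 % was chosen for clinical considerations", and "We claim that a difference of cough occurrence up to 20 % is clinically not relevant". The value 20 % thus appears three times, the last time explicitly as a difference between groups. A margin of 10 points appears nowhere.

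The result fixes the size of the trial: "We decided therefore to include 117 patients per group, to cover the calculated sample size of 19 + 5 patients per group" for superiority and 112 + 5 for noninferiority, 351 in all. The Statistical methods section rests the noninferiority inference on the upper confidence bound and does not give its level. Neither section says whether alpha is one-sided or two-sided.

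**The concern.** For an event expected in 7 to 10 % of patients, a 20-point margin is very wide and should need only a few dozen patients per group. A requirement of 81 to 112 looks like the product of a narrower margin.

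Two things depend on the answer. First, the noninferiority calculation alone explains 117 per group, since superiority needs 19 + 5. If the margin and the calculation disagree, the trial size has no valid derivation as written. Second, the margin is the decision rule, because the upper bound will be compared with it. A margin of 0.20 and one of 0.10 lead to different conclusions from the same data. Noninferiority on airway events is one of the two purposes listed under Objectives and study design.

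**Working it through.** **Inputs (all from Sample size).** Power 0.80; alpha 0.05, sidedness not given, so both readings are tried; cough proportion p = 0.07 or 0.10, taken as equal in the two arms; margin d = 0.20; equal allocation.

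**Formula (Blackwelder, normal approximation).** n per group = (z_alpha + z_beta)² × 2p(1 − p) / d²

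Here 2p(1 − p) = 0.1302 at p = 0.07 and 0.18 at p = 0.10. The squared sum of z-values is (1.645 + 0.842)² = 6.183 at one-sided 0.05 and (1.960 + 0.842)² = 7.849 at one-sided 0.025.

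**Attempt to reproduce 81 and 112.**

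| Margin d | One-sided alpha | p = 0.07 | p = 0.10 |
|---|---|---|---|
| 0.20 (stated) | 0.05 | 6.183 × 0.1302 / 0.04 = 20.1 → 21 | 6.183 × 0.18 / 0.04 = 27.8 → 28 |
| 0.20 (stated) | 0.025 | 25.5 → 26 | 35.3 → 36 |
| 0.10 | 0.05 | 6.183 × 0.1302 / 0.01 = 80.5 → **81** | 6.183 × 0.18 / 0.01 = 111.3 → **112** |
| 0.10 | 0.025 | 102.2 → 103 | 141.3 → 142 |

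Solving for d from the stated sizes gives 0.0997 from 81 and 0.0997 from 112 at one-sided 0.05. At one-sided 0.025 both give 0.112.

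**Other readings of 0.20.**
- Ceiling on the cough rate, d = 0.20 − p, one-sided 0.05: 112 at p = 0.10 but 48 at p = 0.07. This does not explain 81, and the text calls 20 % a difference.
- Relative margin, d = 0.20 × p, one-sided 0.05: 4,107 at p = 0.07 and 2,783 at p = 0.10.
- d = 0.20 with power 0.90 or 0.95, with a continuity correction, with 0.07 and 0.10 as unequal true rates, or counted over two or three arms: none gives both 81 and 112.

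**Power at 112 per group, p = 0.10, no true difference, one-sided 0.05.** The standard error is √(0.18/112) = 0.0401.
- d = 0.20: Φ(0.20/0.0401 − 1.645) = 0.9996 (0.9988 at one-sided 0.025)
- d = 0.10: Φ(0.10/0.0401 − 1.645) = 0.802

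**Effect on the decision (112 per group, one-sided 5 % Wald bound).** The probabilities are from exact binomial enumeration.

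| Situation | Margin 0.20 | Margin 0.10 |
|---|---|---|
| Probability of declaring noninferiority, true 20 % vs 10 % | 0.68 | 0.05 |
| Same, true 14 % vs 7 % | 0.93 | 0.19 |
| Most desflurane coughs that pass when the comparator has 11/112 (9.8 %) | 24 (21.4 %) | 14 (12.5 %) |

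**Both comparators.** At p = 0.10 in all three arms and a margin of 0.10, enumeration gives power of about 0.80 for one comparison and about 0.72 for noninferiority to sevoflurane and propofol together.

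**The case against.** The strongest reply accepts the arithmetic and disputes what follows from it. A reader might infer that the margin is a misprint for 10 %, and that the threshold is therefore twice what the trial was sized for. The document does not support that as a fact. It gives 20 % three times, with a clinical rationale, and never mentions 10 %. Back-solving shows which margin would generate 81 and 112, not which margin was meant. The sponsor may have intended 20 points and miscalculated the sample size. The exact match also needs one-sided alpha 0.05, which is not stated. This objection stands, and it rules out prescribing 0.10 as the only correction. It does not remove the contradiction, because neither sidedness brings a 0.20 margin near 81 and 112.

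It can also be said that a 20-point margin would tolerate a doubling of cough even had the sample size been correctly given as 28, so this is a quarrel with the choice of margin. That is partly right: the protocol gives a reason for its margin, and that reason is not judged here. The decision probabilities serve only to show how much depends on which number applies.

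Finally, cough is a secondary outcome, and under the margin as written the trial is larger than needed, not too small. Both statements are true. They limit the reach of the point, but the derivation of 351 is still unsupported as written.

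**Conclusion.** The point holds as an internal contradiction. With the protocol's own formula and inputs, the stated margin requires about a quarter to a third of the stated sizes: 21 and 28 (or 26 and 36) against 81 and 112. Of the combinations tried, only an absolute margin of 0.10 at one-sided alpha 0.05 returns both figures, which makes it the likely basis of the calculation but does not prove it was the intended margin.

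The consequence is substantial for the noninferiority claim: at 112 per group, a true doubling of cough from 10 % to 20 % would pass about 68 % of the time under one margin and about 5 % under the other. These probabilities assume a one-sided 5 % Wald bound and 112 evaluable patients per group. The primary superiority analysis of emergence time is unaffected, since it needs 19 + 5 per group.

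**What to change.** Reconcile the margin and the calculation before unmasking, by protocol amendment and in the statistical analysis plan that the article promises. State the margin as an absolute risk difference (desflurane minus comparator), with the sidedness of alpha and the level of the confidence bound. Then take one of two routes:

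- **(a) Margin 0.10.** At one-sided alpha 0.05 this preserves the stated alpha, power, cough rates, 81, 112 and 117. Compare the upper one-sided 95 % bound with 0.10 and remove the 20 % statement and its justification.
- **(b) Margin 0.20, if 20 points was truly intended.** Restate the required sizes as 21 and 28 (26 and 36 if alpha is one-sided 0.025) and the power at 112 per group as above 0.999 (0.9988 at one-sided 0.025), and say that 117 per group is not derived from this margin.

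Neither route needs extra patients. Route (a) costs a stricter test, with power of about 0.80 for each comparison and about 0.72 for noninferiority to both comparators at a 10 % cough rate. It also changes the stated threshold after recruitment began in February 2015, so the amendment should record that the decision was made without sight of unmasked results. Route (b) costs the stated rationale for the trial size.

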### Recruitment

Each participating center will recruit in 5 months as many patients as possible according to their clinical routine during the preoperative anesthesia consultation. Before inclusion of study patients, each center must ensure that at least two investigators are available: one physician for the randomization and the intraoperative visit and the second one for the pre- and postoperative visit. The exact time point of the informed consent has to be documented in written form in the patient source data to enable reproducing the sequence of patient recruitment and randomization, in order to prevent selection bias.

### Randomization

The responsible biostatistician will perform a study-specific computer-generated randomization (study arms, number of blocks and block lengths) according to the study-specific biometric specifications, by using the software framework “R” [8]. The complete randomization list and potential block sizes will only be accessible by the biostatistician of the study. To guarantee adequate allocation concealment, the group assignments will be preserved in sequentially numbered, sealed, opaque envelopes and these will be provided to the principle investigator of each center at the beginning of the study by the biostatistician. The principle investigator will ensure that only the unblinded investigators have access to these envelopes and that they will be opened in sequential order of the patients’ surgery time points. Additionally, he will have to assure that the anesthesia is truly performed according to the assigned intervention, to avoid performance bias. In order to maintain blinding during enrollment and data entry to the electronic case report form (eCRF), two different accounts will be created per center. By utilizing the first user account, access to intraoperative data, as well as randomization, will be possible. Using the second account, entry of pre- and postoperative data will be permitted. Patients in compliance with all inclusion criteria and none of the exclusion criteria will be randomly assigned into one of the three study groups: desflurane, or sevoflurane, or total intravenous anesthesia with propofol.

Access to randomization is reserved solely to the intraoperative investigator and has to be done shortly before surgery. The time point of envelope opening, the patient initials and the screening number of the patient will be written on the appropriate envelope before it is opened. The envelopes have to be safely stored in the intraoperative patient file. Within a center, the randomization number will occur in succession. The number will contain information about the randomizing study site and the patient sequence. The randomization number will consist of six digits, the first three for the center and the last three for the patient, for example, 001 to 001 (for center 001 and the first patient included). This randomization code will be used to label all information collected for each patient. The monitors of the study will check carefully that the envelopes were really used in the correct sequence and that the signed informed consent occurred definitively before opening of the randomization envelope.

### Blinding

The trial participant and the investigator performing the pre- and postoperative visits will remain blinded throughout the entire study period. The unblinded intraoperative investigator will ensure that the blinded individual is prevented from recognizing which anesthetic was used, by masking the ventilator with an opaque board before the blinded investigator enters the operating room. The blinded investigator will not have access to the anesthesia records until the study participation of each patient is completed.

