### Participant timeline

A participant chart is shown in Additional file 1. Eligible patients, scheduled for surgery, will be presented to the anesthesia department for the general anesthesia consent preoperatively. Additionally, a blinded sub-investigator will explain the nature and purpose of the study to these patients and seek a written informed consent for the study (time point A, before surgery). The same investigator will collect the following baseline characteristics after the patient enrollment (time point A):AgeSexWeightHeightBMISmoking status (nonsmoker, current smoker-amount of pack years, ex-smoker)Contraceptives (woman - yes/no)Pre-existing diseases and medical/surgical historyClassification according to the American Society of Anesthesiologists (ASA)Apfel ScoreBaseline (Postoperative Quality Recovery Scale) PQRS testing prior to surgery (see Additional file 2)

Shortly before surgery on the same day (time point B), an unblinded investigator will randomize the patients with sequentially numbered, opaque, sealed envelopes (SNOSE).

The same unblinded investigator will perform anesthesia (time point C, surgery) and assess the intraoperative variables in the respective patient:Depth of anesthesia (BIS)Standard safety parameters: ECG, SpO_2_ and end-tidal CO_2_, and NIBPVentilation pressure parameters: Ppeak, Pmean, and PEEPType of performed surgeryRecording of the end-expiratory applied volatile anesthetic concentration/applied amount of propofol for maintenancePharmacoeconomics: Total amount of intraoperative required catecholamines, of additionally applied propofol as rescue medication, of wasted propofol at the end of the surgery in the propofol group and of intraoperative remifentanil and piritramide consumption.Time points of anesthesia induction, LMA insertion, administration of the study treatments, anesthesia and surgery durationFrequency of intraoperative (induction/maintenance) coughs and laryngospasms

The blinded investigator will enter the operating room at the time point T_0_, which starts with cessation of anesthesia and application of maximum fresh gas flow and predefines the measurement start-time point for the time variables. The unblinded investigator will ensure that the blinded individual is precluded from recognizing which anesthetic was used, by masking the ventilator. The blinded investigator will assess the following postoperative variables during time point D:

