### Premature study termination

Participants may withdraw from the study for any reason at any time. As the follow-up period in this study is only one day, we do not expect many withdrawals. These withdrawals could only imply missing data for the PQRS testing at T40 and on 1^st^ POD.

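### The bar on anesthesia records lifts patient by patient, so the assessor of the primary endpoint could learn earlier allocations at a center and guess later ones somewhat better than chance

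*Protocol article*

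**What the plan says.** All references are to the protocol article.

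- **Record access (Blinding).** "The blinded investigator will not have access to the anesthesia records until the study participation of each patient is completed". The release is tied to the individual patient, not to the end of recruitment or to database lock.
- **Length of participation (Premature study termination).** "As the follow-up period in this study is only one day, we do not expect many withdrawals". The last assessment is the recovery scale on the first postoperative day.
- **Who consents (Participant timeline).** "a blinded sub-investigator will explain the nature and purpose of the study to these patients and seek a written informed consent". The same investigator collects the baseline data.
- **Who assesses (Participant timeline).** "The blinded investigator will assess the following postoperative variables during time point D". The list that follows includes TSB, cough at emergence (CE) and laryngospasm at emergence (LSE).
- **Division of roles (Recruitment).** Each center needs "one physician for the randomization and the intraoperative visit and the second one for the pre- and postoperative visit".
- **Sequence (Randomization).** The computer-generated list has blocks. The biostatistician supplies envelopes to each center, to be opened in order of surgery. "Within a center, the randomization number will occur in succession". Block sizes are protected: "The complete randomization list and potential block sizes will only be accessible by the biostatistician of the study".

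**The concern.** In a blocked sequence, past allocations carry information about the next one. Whoever knows the arms already used at a center can guess the coming arm better than one time in three, without knowing the block size, by naming the arm used least so far.

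The Blinding rule opens that information to the wrong role. Once a patient's day-one contact is done, nothing in the article keeps that patient's anesthesia record from the person who will time TSB in the center's next patients. TSB is taken by stopwatch with a command repeated every 20 seconds, so the assessor has some influence on it. The Discussion accepts that the anesthetist cannot be blinded and relies on this second investigator to limit detection bias.

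The stated safeguards are the masked ventilator, sealed envelopes, two separate eCRF accounts, concealed block sizes, and consent before the envelope is opened. They protect the current patient's allocation and the randomization data. None closes the anesthesia records of patients who have finished.

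**Working it through.** The plan gives no figure on this point, so there is none to reproduce. The check sizes how much a reader of completed records could gain.

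**Inputs from the article**
- 351 patients, three equal arms (Sample size); four centers (Study setting). With equal recruitment, which is an assumption, 351/4 = 87.75, about 88 per center.
- Recruitment over 5 months per center (Recruitment), or about 7 months from end of February to September 2015 (Trial status).

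**Assumptions**
- The block length is not given. Permuted 1:1:1 blocks of 3, 6, 9 and 12, and random mixes, were tried.
- A separate blocked list per center is inferred from the envelopes and numbering by center.
- The guess is the arm with fewest known past allocations, with ties broken at random.
- Lag is the number of most recent patients whose records are still closed.

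**Block of 3, by hand**
- Lag 0: the chances at positions 1, 2 and 3 are 1/3, 1/2 and 1. The mean is (1/3 + 1/2 + 1)/3 = 11/18 = 61 %.
- Lag 1: only position 3 gains, because one arm of the current block is known. The mean is (1/3 + 1/3 + 1/2)/3 = 7/18 = 39 %.
- Lag 2: nothing in the current block is known. The result is 1/3 = 33 %.

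**Simulation, 88 patients per center, 1,000 sequences per setting (share of correct guesses)**

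| Block size | Lag 0 | Lag 1 | Lag 2 |
|---|---|---|---|
| 3 | 60.8 % | 38.8 % | 33.4 % |
| 6 | 55.5 % | 44.8 % | 40.4 % |
| 9 | 52.5 % | 45.4 % | 42.1 % |
| 12 | 50.6 % | 45.1 % | 42.7 % |
| mix 3/6 | 57.4 % | 42.8 % | 38.1 % |
| mix 6/9/12 | 52.5 % | 45.2 % | 42.2 % |

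Chance is 33.3 %. The simulated row for blocks of 3 agrees with the hand calculation.

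**Which lag is realistic?** Take 21 working days a month (an assumption). The rate per center is 87.75/(5 × 21) = 0.84 patients per working day, or 87.75/(7 × 21) = 0.60. If patients arrive independently, a given patient has on average half that rate operated on earlier the same day, which is 0.30–0.42. If the previous day's patients have not yet had their day-one contact, one full day's rate is added, giving 0.90–1.25. So at the assessment of TSB a lag of 0 to 1 is typical, and 2 will occur on busy days. At consent the lag is longer, because every patient operated on between the consultation and the patient's own surgery adds to it.

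**After the fix.** With no completed records open, this source of past allocations is gone and the guess returns to 33.3 %.

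**The case against.** **The rule sets a minimum and is not an instruction.** It does not direct anyone to read records, and using it would mean retrieving and tallying the center's earlier cases. This stands: opportunity is shown, use is not. But a blinding rule exists to remove the opportunity, and this one expires while the center is still recruiting.

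**The sentence could mean all patients.** That is possible but less natural, and the ambiguity would itself need repair.

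**A reader might infer that the section contradicts itself**, because it also says that the participant and this investigator "will remain blinded throughout the entire study period". The documents do not support this. Data collection methods and Statistical methods both use the same period for a single patient, and on that reading the two sentences agree.

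**A reader might also infer that some allocations become certain in advance.** That needs known block boundaries and no closed record. Block sizes are withheld from the sites. Even with the boundaries known, one closed record cuts the certain share to 0–3 %, and two cut it to at most 0.5 %.

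**Selection at consent is limited.** Consent precedes surgery and envelopes follow surgery order, so the consenting person only partly controls who comes next. The screening log must give reasons for not enrolling eligible patients, consent times are documented, and monitors check the envelope sequence. This largely stands. It does not answer the assessor-blinding point, because the order is already fixed when TSB is timed.

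**TSB has a defined start and fixed command intervals.** This narrows the room for assessor influence but does not remove it.

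**Conclusion.** The point holds as a weakness in a stated rule. The embargo on anesthesia records ends patient by patient, while the same role continues to assess the primary endpoint in a blocked sequence at the same center.

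The realistic gain is moderate: about 39–45 % correct guesses with the latest record closed and 33–43 % with the latest two closed, against 33 % by chance. With blocks of 3 and two records closed there is no gain. The 51–61 % figure is an upper bound that needs every earlier record open. All these figures rest on assumed blocks of 3 to 12, an inferred list per center, and equal recruitment.

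The main exposure is the blinding of the assessor of TSB, CE and LSE; selection bias is the lesser route. No effect on TSB has been estimated, and the article gives no evidence that records will be read. The change is worth making because it is cheap and protects the safeguard on which the Discussion relies.

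**What to change.** Replace the last sentence of the Blinding section with: *Investigators performing pre- and postoperative visits will have no access to the anesthesia records of any study patient until recruitment and outcome entry at the center are complete (or database lock), except for emergency unblinding.*

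The emergency route in Unblinding procedures stays as it is. Envelopes and the intraoperative eCRF account are already restricted under Randomization and need no new rule.

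The cost is one sentence and a line in site training; the downside is that this role sees the records later. Where staffing allows, a center may also be advised not to use someone from the unblinded role as blinded assessor for later patients. This should remain a recommendation: nothing in the article says that people swap roles, and a fixed rule could strain centers that enroll as their logistics permit.
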